## Abstract

**Aims:**

The concept of prehabilitation, defined as interventions aimed at enhancing a patient's functional capacity prior to an impending physiological stressor, may contribute to reduced postoperative morbidity and mortality. The study's goal is to verify or refute the feasibility of a prehabilitation programme for two diagnostic patient groups during neoadjuvant chemo(radio)therapy, which is prescribed before the scheduled surgical procedure. This is a single group study design, with all patients enrolled receiving the intervention.

**Methods:**

This is an interventional feasibility study of a prehabilitation programme in the form of physical training conducted at home. The training consists of progressively dosed walking and strength exercises for selected muscle groups. Data will be monitored telemetrically and also through telephone contact with participants. Primary outcomes include: the percentage of patients interested in participating in the study out of all patients indicated for neoadjuvant therapy at University Hospital Ostrava during the observed period, the percentage of patients who complete the prehabilitation programme until the date of surgery and individual patient compliance. Secondary outcomes include physical fitness parameters obtained from cardiopulmonary exercise testing, grip strength measured by a dynamometer, changes in body composition, EORTC QLQ-C30 quality of life questionnaire, and a questionnaire on the subjective perception of the exercise programme. Both primary and secondary outcomes will be compared between study arms (two diagnostic groups). The study is registered at ClinicalTrials.gov, ID: NCT05646043.

**Conclusion:**

The results of this study can serve as a foundation for larger, multicentre, controlled studies in the future.

## Introduction

Curative treatment of the cancer of upper gastrointestinal tract (oesophagus, oesophago-gastric junction, and stomach) and treatment of rectal cancer is multimodal. Neoadjuvant chemotherapy, radiotherapy, or chemoradiotherapy (further referred to as neoadjuvant therapy) is commonly indicated during the preoperative period in order to achieve downstaging, downsizing, and to reduce the risk of recurrence.

Oncological treatment has a negative impact on the overall physical and mental condition of patients; their quality of life and daily activities are reduced (1). Neoadjuvant therapy is associated with a reduction in cardiopulmonary function among patients undergoing oesophagectomy (2). The decline in cardiorespiratory reserve following neoadjuvant chemotherapy in individuals with oesophagogastric cancer is observed to persist up to the time of surgery (3, 4). The surgical procedures performed are both demanding and prolonged, imposing a significant burden on patients. Furthermore, the duration of surgery correlates with a statistically significant increased risk of complications, including wound infection, dehiscence, hemorrhage, and pneumonia (5).

In the traditional care model, most patients receive rehabilitation in the postoperative period. The rehabilitation aims to improve overall physical fitness, regain self-care abilities, and return to activities patients were able to do before the oncological diagnosis, including returning to their profession and hobbies. One of the main aim of early rehabilitation in postoperative time is to improve the mobility of the patient. Mobilization soon after surgery has a positive effect on recovery of function and therefore it is a part of ERAS (Enhanced Recovery After Surgery) programmes (6). ERAS is becoming a standard part of clinical practice, positively contribute to reducing the risk of postoperative complications, and shortening the length of stay (7–9). Despite the positive effect of ERAS measures, especially the surgery of the upper gastrointestinal tract, is still associated with a high morbidity and mortality. Cardiopulmonary fitness and muscle strength are reduced in these patients; they suffer from fatigue, anxiety, depression, and have lower quality of life (1, 10–14). These accompanying problems negatively influence the therapeutic process, and therefore, lately, attention and efforts to improve postoperative outcomes are increasingly focusing on the period before surgery.

The concept of prehabilitation, which is defined as an intervention improving an individual's functional capacity before an upcoming physiological stressor (15, 16), might be a way to improve outcomes. The prehabilitation is commonly multimodal, with the main components being physical exercise, nutritional interventions and psychological coaching (17). Despite the inconclusive evidence regarding the efficacy of prehabilitation, programmes are increasingly being integrated into clinical practice. A randomized controlled trial published in 2022 demonstrated that patients undergoing prehabilitation prior to oesophagogastric cancer resection exhibited greater retention of cardiopulmonary fitness, muscle mass, and quality of life compared to those receiving standard care (18).

Furthermore, several studies indicate a significantly lower incidence of complications among the prehabilitated cohort, alongside reduced hospital stays and enhanced functional capacity (19–24). An umbrella review of systematic reviews concerning prehabilitation for surgical patients highlights low to very low certainty evidence supporting a reduction in complications and length of stay in cancer surgery. Additionally, moderate certainty evidence indicates improvements in functional recovery, while low to very low certainty evidence suggests that nutritional prehabilitation may mitigate the risks of complications, mortality, and length of stay (25).

The positive influence of physical activity and exercise is undeniable. Physical activity reduces the risk of cardiovascular diseases (26), type II diabetes (27), and cancer (28). On the contrary, physical inactivity is directly related to mortality (29). Physical activity prior to cancer diagnosis (30), but also after oncological treatment affects survival (31) and might be associated with disease recurrence (32). Regular exercise leads to the body's adaptation to physical stress and increases fitness. Although scientific interest in prehabilitation is on the rise, there are many ambiguities and questions that must be answered. The 15-week programme for patients prior to oesophagogastric cancer resection, consisting of aerobic, resistance, and flexibility training, included twice-weekly supervised one-hour exercise sessions combined with thrice-weekly one-hour home exercises and a nutritional and psychological intervention. This approach has been shown to improve cardiopulmonary fitness, muscle strength, and quality of life (QOL) as previously mentioned (18). Ten week supervised training programme (aerobic exercise, muscle strength and endurance) et dose 150 min per week may enhance physical function during neoadjuvant treatment in rectal cancer patients (33). There is not enough scientific evidence whether programmes carried out under direct expert supervision are more effective than those done by the patient independently at home.

These questions should be answered before prehabilitation programmes become a standard part of clinical practice. Not only for this reason, authors decided to conduct the study presented here.

## Methods

This is a feasibility study focused on patients with oesophagogastric cancer or rectal cancer who were, based on the decision of the multidisciplinary team (MDT) of the University Hospital in Ostrava (FNO), indicated for neoadjuvant therapy in the preoperative period.

These groups of patients were chosen as they are commonly treated with neoadjuvant treatment, which opens a time window for the application of a prehabilitation programme. The prehabilitation programme is designed in the form of physical training aimed at improving or retaining cardiorespiratory fitness as well as the strength of selected muscle groups. Each patient also receives nutritional support. The programme is designed to minimise significant time demands on medical staff, so it will be implemented in the patient's home environment. The study aims to answer question whether the selected patients will be able to complete a home exercise regimen during the preoperative period when they undergo neoadjuvant therapy.

The primary outcomes to evaluate the feasibility of the study are:
1.Percentage of patients who consent to participate in the study out of all diagnosed and for neoadjuvant therapy indicated patients in the monitored period. The reasons for refusing to participate will be recorded.2.The percentage of patients who consent to participate in the study and who remain participants until the end of the study period, out of all consented patients.3.Individual patient compliance—defined as the number of days the patient wore a smart bracelet, carried out or attempted to complete the prescribed exercise programme (aerobic exercise and strength training), and remained accessible for follow-up telephone contact, out of the total number of days in the observed period.4.All adverse events related to the prehabilitation programme implementation.

Secondary outcomes include changes in physical fitness parameters obtained from cardiopulmonary exercise testing CPET—peak oxygen uptake, anaerobic threshold test performed on a Bicycle ergometer ERGOSELECT 5 (Ergoline GmbH, Bitz, Germany and COSMED srl, Rome, Italy) using a ramp protocol with a gradual increase in load of 0.5 W per kilo per min, changes in grip strength measured by hand dynamometer, changes in body composition, Borg's scale of perceived exertion, changes in health-related quality of life measured by EORTC QLQ-C30 quality of life questionnaire, and a subjective perception of the exercise programme.

Inclusion criteria for this study are age >18 years and planned resection for locally advanced oesophagogastric adenocarcinoma or adenocarcinoma of rectum with planned neoadjuvant therapy and ability to complete CPET and able to sign informed consent for study participation. Exclusion criteria for this study are contraindications to CPET or inability to perform CPET or daily exercises due to orthopaedic limitations (e.g., amputation, severe gonarthrosis, coxarthrosis) or inoperability determined by the MDT decision or synchronous malignant disease or multivisceral resection or planned non-surgical therapeutic procedures.

The sample size was set at 40 patients given the feasibility nature of the study (34). The patient will be referred to oncologist once MDT agrees on the therapeutic plan. The oncologist, overseeing the oncological treatment, will inform the patient about the possibility of participating in the study and if patient agrees to participate in the study, informed consent will be signed before start of the neoadjuvant therapy.

The length of the prehabilitation programme is based on the length of oncological treatment which for group of patients with oesophagogastric adenocarcinoma consists of four cycles of neoadjuvant chemotherapy at 15-day intervals for a total length of 60 days. The restaging time takes 14–21 days, and time from restaging to surgery usually takes 7–14 days. The total duration for the prehabilitation programme for this group of patients will be about 11 to 13 weeks. For rectal adenocarcinoma, the oncological treatment involves 4–5 weeks of chemo(radio)therapy, followed by restaging after a 3–4 week interval and followed by surgery 1–2 weeks later. The total duration of the programme for this diagnostic group will be around 8 to 11 weeks (Figure 1).

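### Primary outcome 1 counts consenters against all patients indicated for neoadjuvant therapy, so it measures reach and cannot by itself separate ineligibility from refusal

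*Protocol article*

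**What the plan says.** The Methods section of the protocol article defines the first primary outcome as the percentage of patients who consent "out of all diagnosed and for neoadjuvant therapy indicated patients in the monitored period", and adds that reasons for refusal are recorded. The Abstract gives it as the "percentage of patients interested in participating in the study out of all patients indicated for neoadjuvant therapy at University Hospital Ostrava". Neither place limits the denominator to patients who meet the entry criteria or who were approached.

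The same Methods section admits only adenocarcinoma and requires that the patient can complete CPET. It excludes patients with "contraindications to CPET or inability to perform CPET or daily exercises due to orthopaedic limitations", and also those with "synchronous malignant disease or multivisceral resection or planned non-surgical therapeutic procedures". The treating oncologist "will inform the patient about the possibility of participating in the study".

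The Abstract says that primary as well as secondary outcomes will be compared between the two diagnostic groups. Statistical methods says that primary outcomes are reported as counts and percentages.

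**The concern.** A patient can be indicated for preoperative neoadjuvant therapy and still be barred from the study. Such a patient counts in the outcome exactly as a patient who was invited and declined. The percentage therefore has a ceiling below 100% whenever anyone in the denominator is ineligible, even if every eligible patient accepts.

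Two uses of the figure suffer:

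- **Planning later trials.** The article hopes the results will support larger multicentre controlled studies. Low uptake among eligible patients calls for a different response from high uptake under narrow criteria.
- **Comparing the diagnoses.** If the exclusions fall unequally on oesophagogastric and rectal patients, a gap in eligibility will look like a gap in willingness.

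The numerator also shifts between the two places: interest in the Abstract, consent in Methods. These are different counts.

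**Working it through.** **No plan figure to reproduce.** The article states no expected or target value for outcome 1. Its only design figure, 40 patients, is justified by the feasibility purpose and a citation, without a rate or precision from which to rederive it.

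**Which restrictions matter.** Each entry criterion is set against the population that opens the Methods section: patients with oesophagogastric or rectal cancer whom the multidisciplinary team (MDT) has indicated for preoperative neoadjuvant therapy.

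| Restriction | Can the patient still be in the denominator? |
|---|---|
| CPET contraindicated or not possible | Yes |
| Orthopaedic limitation | Yes |
| Synchronous malignancy | Yes |
| Multivisceral resection | Yes |
| Not adenocarcinoma | Yes, since that opening sentence speaks of cancer in general; no, if the denominator is meant to be adenocarcinoma only, as the Conclusion describes the groups |
| Inoperable, or non-surgical treatment planned | Largely no, as these patients are not being treated ahead of surgery |

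The first four rows are enough to establish the point.

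**Formula.** Let e be the share of indicated patients who are eligible, o the share of eligible patients offered the study, and w the share of those offered who consent. Then

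- outcome 1 as defined = consented / indicated = e × o × w
- uptake = consented / (eligible and offered) = w

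The article gives none of the three shares. All values below are assumptions.

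**Same willingness, different reported percentage** (w = 0.70; 40 consenters, so 40 / 0.70 ≈ 57 eligible patients offered):

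| e | o | Indicated = 40 / (e × o × w) | Outcome 1 | Uptake |
|---|---|---|---|---|
| 1.0 | 1.0 | 57.1 | 70% | 70% |
| 0.8 | 1.0 | 71.4 | 56% | 70% |
| 0.6 | 1.0 | 95.2 | 42% | 70% |
| 0.5 | 1.0 | 114.3 | 35% | 70% |
| 0.8 | 0.8 | 89.3 | 44.8% | 70% |

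**Same reported percentage, different willingness.** With o = 1, w = outcome 1 / e. A reported 40% fits e = 0.5 with w = 0.8 (0.5 × 0.8 = 0.40) and equally e = 0.8 with w = 0.5 (0.8 × 0.5 = 0.40). In the first case four in five eligible patients accept under narrow criteria; in the second, half decline.

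**Between diagnoses.** If both groups had w = 0.70 and o = 1, but e were 0.8 in one and 0.6 in the other, outcome 1 would read 56% against 42%. That is a 14-point difference with no difference in willingness.

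**What the refusal record adds.** If every refuser is logged, consented / (consented + refused) can be derived. In the example with 57.1 offered, there are 57.1 − 40 = 17.1 refusers and 40 / 57.1 = 70%. What remains, indicated minus consented minus refused, is a single block in which ineligible patients and any not approached are not told apart.

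**The case against.** The strongest reply is that consenters over all indicated patients is a legitimate quantity. It says what share of the clinic's target population the programme reaches, and the article never calls it willingness. Moreover, refusals are recorded, no decision rule or sample size depends on this outcome, and the central question of whether patients can complete the regimen is addressed by outcomes 2 and 3, which do not use this denominator. All of this stands, and it is why the point is one of interpretability rather than error.

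It does not remove the point. The refusal record allows only a partial separation, and no percentage based on it is defined as an outcome. The Abstract's promise to compare primary outcomes between diagnoses invites a reading in terms of willingness that the ratio cannot carry.

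A condensed article may also leave a screening log to the full protocol, so its absence is not held against the plan. The point rests on the stated definition.

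Stronger readings are tempting, but the documents do not support them:

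- *Eligible patients go unoffered.* Nothing says so. The article states that the oncologist informs the patient. The offered share appears above only because the denominator is everyone indicated.
- *The denominator covers every cancer treated at the hospital.* The Abstract's phrase taken alone could suggest this, but the Abstract itself speaks of two diagnostic groups and Methods restricts the study to them.
- *Every exclusion criterion dilutes the figure.* Inoperable patients and those with planned non-surgical treatment largely fall outside the denominator already.

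**Conclusion.** The point holds as a matter of definition. The only participation percentage defined combines eligibility with consent, and so would a comparison of it between the two diagnoses.

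Its size in this trial cannot be stated, because the article gives no eligible share. Over assumed eligible shares of 50% to 100%, with all eligible patients offered the study, 70% willingness would be reported as anything from 35% to 70%. If nearly all indicated patients are eligible, the gap nearly vanishes.

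A reader might infer that outcome 1 is invalid or must be replaced. It need not be: the ratio is sound as reach and only needs a companion. This is a cheap improvement, not a must-fix.

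**What to change.** 1. Keep consented / all indicated, with the denominator stated as oesophagogastric or rectal patients, and label it reach. Say whether non-adenocarcinoma patients are counted.
2. Add consented / (eligible and offered) and label it uptake.
3. Report the counts indicated, eligible, offered and consented for each diagnosis.
4. Use uptake, not reach, for any between-diagnosis statement about willingness.
5. Use consent as the numerator in the Abstract as well as in Methods.

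The cost is a few log fields for MDT-indicated patients who are not enrolled, plus wording changes in two places. No further patients, visits or procedures are needed. Eligibility and offer status are best logged as patients are discussed, since they may be hard to reconstruct later.

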## Intervention

### Prehabilitation programme

In addition to psychological and nutritional support, which is a standard part of cancer treatment, the foundation of the prehabilitation programme is physical training. The nutritional support of probands enrolled in the study is similar to that of other cancer patients. Every patient is screened and assessed by a dietitian for potential nutritional supplementation as part of the standard care. This is followed by tailored dietetic advice regarding food, protein, energy intake, and supplementation. In some cases, patients may require enteral or parenteral feeding, which is occasionally administered through adjuncts such as nasoenteric tubes, feeding jejunostomies, or, in rare instances, total parenteral nutrition.

Even before starting neoadjuvant therapy, during the first clinical examination, the patient will be thoroughly educated about the prehabilitation programme, and they will be given an exercise diary to record their daily physical activity.

The initial examination will include an assessment of the overall condition, including obtaining past medical history and testing grip strength. Validated InBody230 body composition analyser (Biospace Co., LTD., Coalville, United Kingdom), which fulfils the standards of IEC60601-1(EN60601-1), will be used to analyse body composition (percentage of water, fat, muscle mass). Patients will be educated on the use of technologies that will record monitored parameters (steps, heart rate, weight), and they will be given a telemetry set—a MiBand 5 pedometer (Xiaomi Inc, Beijing, China), a Galaxy A13 mobile phone (Samsung Electronics, Suwon, South Korea), a W62 telemetry scale (Zhongshan Loease Electronic Technology Co, Ltd, Zhongshan, China), and an initial CPET will be performed.

For one week, the patient's physical activity will be monitored telemetrically by recording the number of steps. Based on this, a baseline value will be established, from which the subsequent exercise dosage will be derived.

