### Physical training

Physical training will consist of endurance (walking) and strength components. Walking is the most natural physical activity for humans. The training programme aims to be individualised by the research team. The basis for determining the number of steps per day is the baseline value for each patient. This will be increased by 10%–15% every week until the date of surgery. If the increase is not tolerated by the patient, the last increased step count will be retained, and consideration of further increase will be postponed until the following week. The expected total increase in steps is 120%–180% of the baseline. The authors are aware that not every patient can achieve these values. Within the feasibility study, the authors want to verify the acceptable dosing of the load. At the same time, authors' goal is for the patient to perceive their load at medium intensity (measured by the Borg scale, corresponding to 3–4 out of 10) for 30 min per day.

Strength training will be applied using exercises to strengthen the upper (biceps and triceps groups through exercises without and with dumbbels or rubber expander, wall push ups) and lower limbs (strengthening of gluteal, quadriceps, hamstrings and culf muscles through squats with or without back support, standing up from a chair, toe raises, leg raises) and the core. Training will involve a set of eight exercises in several difficulty variations. The patient chooses a variant that he or she can perform and gradually can choose a more difficult variant of the exercise. Each exercise will be done for one minute. The set will be repeated twice. The total strength training time will take approximately 20 min. The patient will perform this set seven days a week. Achievement of Borg 3–4 for strength training is not required. A description of each exercise and photo documentation is part of the exercise diary. The patient is also taught about possible mistakes when performing each exercise and the mistakes are photo documented. The education in the training program is part of the first clinical examination.

If interested, the patient can undertake additional activities (running, cycling, etc.) during the study. Patients will be encouraged to do these activities, and these will be recorded.

Patients will record their daily physical activity in their exercise diaries (number of steps per day, strength training, subjective perception of intensity according to Borg, other physical activities).

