Physical training will be carried out throughout the neoadjuvant therapy and will continue after its completion, up to 1–2 weeks before surgery.

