### Data monitoring

Data collection will be obtained in two ways: by contacting patients by phone and by remote monitoring. During physical training, the patient will be contacted by phone once a week by the study researcher to support them, monitor data from the exercise diary (number of steps per day/week, number of days per week performing strength exercises, subjective perception of intensity according to the Borg scale during aerobic activites, other physical activities from the previous week). During the conversation, any patient difficulties and problems will be discussed. The patient will have the opportunity to participate in specifying the physical load (number of steps) for the following week.

Remote monitoring will be ensured in collaboration with the telemedicine services centre. Patients will be equipped with the aforementioned telemetry set to ensure data capture. Data will be transmitted continuously to the research team and evaluated once a week before a phone call with the patient.

The telemedicine service centre also includes a control centre, which will monitor threshold and critical values, track trends of measured values, identify and display incidents (alerts and alarms), generate reports, secure store and archive data, transfer data from client terminals to the monitoring centre, and provide technical support to system users.

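### Primary outcome 3 merges bracelet wear, done-or-attempted exercise and telephone reachability over an unbounded period, so it cannot by itself show whether patients complete the regimen

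*Protocol article*

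**What the plan says.** The Methods section of the protocol article states the study question as "whether the selected patients will be able to complete a home exercise regimen", and the Conclusion calls this the basic research question. There are four primary outcomes: consent, retention, individual compliance and related adverse events.

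Compliance is a number of days. A day counts if the patient wore the bracelet, "carried out or attempted to complete the prescribed exercise programme (aerobic exercise and strength training), and remained accessible for follow-up telephone contact". The denominator is given as "out of the total number of days in the observed period". The article does not say when that period starts or ends.

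Four other statements bear on the definition:

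- **Frequency of exercise.** For strength training, "The patient will perform this set seven days a week" (Physical training). Walking has a daily step target revised weekly.
- **Telephone contact.** During training, "the patient will be contacted by phone once a week by the study researcher" (Data monitoring).
- **End of training.** The Physical training section ends by saying that training continues "up to 1–2 weeks before surgery", and the section on termination agrees. Earlier in Physical training, however, the weekly step increase continues to the day of surgery, and the Abstract also describes the programme as running to that day.
- **Start.** "For one week, the patient's physical activity will be monitored telemetrically by recording the number of steps" (Prehabilitation programme). The step dose is derived only after that week.

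**The concern.** The outcome is meant to show whether the exercise gets done, but it puts three different behaviours into one number: device use, exercise and reachability. Within the exercise part, a session begun and abandoned earns the same credit as a full one, and no minimum is set for an attempt. A high percentage could therefore come from patients who complete nearly every session or from patients who complete few.

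The denominator adds a second difficulty. If it includes days on which no training was prescribed, a fully adherent patient cannot reach 100%, and the shortfall depends on programme length, which differs between the two diagnostic groups. The Abstract says that primary outcomes will be compared between those groups.

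At stake is what a later controlled trial can take from this study. It would need to know how much of the prescribed exercise patients manage, and, separately, whether they wear the device and answer calls.

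**Working it through.** **1. Which primary outcome addresses the question?** Outcome 1 counts consent, outcome 2 counts patients still in the study at its end, and outcome 4 counts adverse events. The Abstract words outcome 2 as completing the programme, but Methods defines it as remaining a participant, which is retention. Only outcome 3 measures exercise done.

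**2. Attempts.** The exercise component equals (days completed + days attempted only) / days. A patient who starts every session and finishes none scores 100% on it. As an illustration with assumed figures, 40% of days completed plus 50% attempted only gives 40 + 50 = 90%.

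**3. Telephone condition.** There is one scheduled contact per 7 days. The text gives no rule for turning a missed call into days. If it costs one day, the loss is 1/91 = 1.1 points over 13 weeks or 1/56 = 1.8 points over 8 weeks. If it costs the whole week, the loss is 1/13 = 7.7 or 1/8 = 12.5 points. This problem is confined to the telephone component: bracelet data are transmitted continuously and the diary is daily.

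**4. Stated programme lengths (Methods).**

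- Rectal: (4–5) + (3–4) + (1–2) = 8–11 weeks, matching the article exactly.
- Oesophagogastric: 60 + (14–21) + (7–14) = 81–95 days = 11.6–13.6 weeks, against a stated length of about 11 to 13.

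Both sums run from the start of oncological treatment to surgery.

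**5. Highest possible score for a patient who trains on every prescribed day.** With W the stated length in weeks and s the weeks between end of training and surgery, the ceiling is (W − s)/W if the observed period runs to surgery.

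| Group | W | s = 1 | s = 2 |
|---|---|---|---|
| Rectal | 8 | 7/8 = 87.5% | 6/8 = 75.0% |
| Rectal | 11 | 10/11 = 90.9% | 9/11 = 81.8% |
| Oesophagogastric | 11 | 10/11 = 90.9% | 9/11 = 81.8% |
| Oesophagogastric | 13 | 12/13 = 92.3% | 11/13 = 84.6% |

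If the observed period is the training period, the ceiling is 100% in both groups.

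**6. Baseline week, if it is counted.** Its position relative to the stated lengths is an assumption.

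- Inside them, (W − s − 1)/W: 62.5–81.8% (rectal) and 72.7–84.6% (oesophagogastric).
- Before them, (W − s)/(W + 1): 66.7–83.3% and 75.0–85.7%.

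**The case against.** The best defence is that crediting attempts is an open and sensible choice for a titrated home programme. Patients pick a strength variant they can manage, step increases that are not tolerated are held, and the authors say that not everyone will reach the targets. Engagement is a legitimate feasibility measure. Step counts and strength days are also collected, and change in steps is tested. All of this stands. It means that the limitation lies in the summary figure, not in the study's data; a reader who concludes that the trial as a whole cannot show completion goes too far.

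Several other stronger readings are tempting but not supported:

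- **That compliance is capped below 100%.** The period is undefined, and the article ties calls and diary review to the time of physical training, so the training period is a natural reading. The full protocol or the study diagram, which is not shown, may settle it. The 75% floor also pairs the shortest rectal programme with the longest stop. If the stop is assumed to equal the restaging-to-surgery interval, the rectal range is 7/9 = 77.8% to 9/10 = 90.0%.
- **That diagnostic groups will differ artificially.** With a 2-week stop the ceilings differ by 84.6 − 75.0 = 9.6 points at the extremes of 13 and 8 weeks, but by nothing when both programmes last 11 weeks or when only training days count.
- **That reachability is known on only 1 day in 7 (14%).** Remaining reachable can be a status that one call establishes for the week. No section requires a daily call.
- **That exercise without the bracelet always fails.** This needs all conditions to hold on the same day. The sentence can also be read as listing separate day counts.
- **That training certainly stops 1–2 weeks before surgery.** The article says both this and that the programme runs to surgery.

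No success threshold is attached to compliance, so no pass-or-fail decision turns on it. That lowers the stakes, but the figure is still the only primary evidence on the study's own question.

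**Conclusion.** The concern holds in a limited form. The firm part needs no assumption: the stated rule scores attempted and completed days alike, while the stated aim is completion, and no other primary outcome fills the gap. Followed exactly, outcome 3 could report high compliance with little completion. The telephone condition is a poor fit to a day count, because the only scheduled check is weekly and no conversion rule is given.

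The denominator part is conditional. The ceilings of 75–91% (rectal) and 82–92% (oesophagogastric) apply only if the observed period runs to surgery and training ends 1–2 weeks before it. The lower figures also need the baseline week to be counted. What is certain is that the article leaves the limits open and contradicts itself on when the programme ends.

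A reader might infer that compliance will be overstated, or that it will be understated. Neither follows: credit for attempts pushes the figure up and non-training days push it down, so the net bias cannot be signed.

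**What to change.** Keep the engagement figure (done or attempted) if it is wanted, and report beside it:

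1. for walking and for strength separately, days completed as prescribed and days attempted only, each divided by days with a prescription in force;
2. bracelet-wear days out of days the bracelet was issued;
3. weekly calls answered out of calls scheduled.

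Define the first and last day of the observed period as the prescribed training days. Reconcile the Abstract, the durations in Methods and the step-progression rule in Physical training with the end of Physical training and the termination section. This review takes no view on which end date is right.

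The cost is mainly wording. The completed-day rate will probably be lower than the present figure. Daily steps are already captured, but the article lists only strength training in the diary and the number of days it was performed in the weekly call. It does not show full and partial sets recorded separately, so one tick-box in the diary or call form may be needed.
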